### 4.2. Data Management

Clinical trial data (F_clin_, W_clin_) will be collected and stored in pseudonymized form. The allocation of person and pseudonymized code will only be possible via an allocation list, stored securely and separately from the coded research data. The research data collected by the case report forms will also be kept secure. The electronic data will be stored on password-protected computers, and backup copies will be made regularly and stored securely. The allocation list and the coded research data will only be accessible for the study director and the study staff, and they will be obliged by signature to maintain confidentiality about the data collection of the clinical trials. The system usage data will be collected and stored pseudonymously by VHG [71].

The DoSS will only transmit the pseudonymized research data to SEVERA via a secure cloud system for combined data analysis of the online and the clinical trials. VHG will transmit the pseudonymized system usage data to SEVERA and the DoSS. No data will be shared with any third parties. SEVERA and the DoSS will carry out the data analysis of the clinical trials. The results of the clinical trials will only be presented and published in aggregated form so that no conclusions can be drawn about individuals. All personal data of the clinical trials will be deleted three years after study completion. Finally, all clinical trial research data will be deleted after ten years.

All personal data of the clinical trials will be stored securely and separately from the research data. Personal data will not be published or passed on to third parties. The personal data entered on the project’s landing page for trial registration will be accessed by the study director via a back-office system of VHG. The study participants will agree to this by their written consent form. After completion of study enrolment, the back-office system will be immediately shut down, and the DoSS will securely store the data. Personal data of excluded subjects will be deleted immediately during the screening process.

Participation in the clinical trials and the health programs will be voluntary. The study participants will be able to withdraw participation at any time without giving reasons or incurring any disadvantages. They will be able to withdraw on their own via the health program or by informing VHG or the DoSS. In addition, the principal medical investigator of the study will be able to terminate participation prematurely if health impairments occur that partially or entirely exclude the ability to participate in the trial or the health program. In such a case, the personal data will be deleted immediately. The research data already collected will be stored anonymously and included in analyses and publications. No further data will be collected. The same procedure will be applied if participants continue participating in the health program despite withdrawing from the trial.

The participants will be informed about all data protection concerns of the clinical trials and will provide written consent. A data protection concept following the European Union General Data Protection Regulation (GDPR-EU) was developed between all project partners (SEVERA, DoSS, VHG) for the evaluation project. This includes a Joint Controller Agreement (JCA) signed by all project partners and data protection officers [71].

The blood samples will be the only biomaterials of the clinical trials. The MVZ Clotten in Freiburg will analyze and properly dispose of the blood samples.

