#### 2.3.2. Non-Interactive Web-Based Health Program

The program for the control group for both clinical trials (F_clin_, W_clin_) will consist of a simply designed online platform that offers support in increasing physical activity and physical fitness (F_clin_) or losing and maintaining weight (W_clin_) over a 12-week intervention phase. In terms of content, it consists of a health-related knowledge transfer. Thus, only scientific background information on the respective health goal can be found, structured in short articles, but without interactive components. In addition, the user has access to personal data and the study information and consent form for the online and the clinical trial and has the option to withdraw participation from the trials and the health program.

The study participants of the clinical trials (F_clin_, W_clin_) will receive the respective health program after successful baseline assessment. They will log into the program via the project’s landing page. Criteria for discontinuing, interrupting, or modifying the allocated intervention are defined as feeling unwell, worsening health status, illnesses, diseases, injuries, harms, adverse events, or withdrawal from participation. These criteria will be determined by the study participant or the principal medical investigator of the study. Apart from the interventions, the participant will not be allowed to participate in other studies on physical activity or dietary behavior. For successful study participation and to promote adherence, the study participants will get free medical examinations and an activity tracker (Fitbit Charge 3^TM^) [74]. For participating in the online trial, they will obtain a shopping voucher and discount coupons. Apart from that, all study participants will be given free access to the current version of the TK-HC, including all coaching modules after study completion. As the TK-HC was frozen as a study version before the study started, the current version of the TK-HC contains some new content or features as it is continuously developed [71]. To maintain adherence during the study course, the study participants of the clinical trials will be reminded of the medical examinations by telephone and e-mail. To further monitor adherence, usage behavior data on the health programs will be analyzed within the formative evaluation of the online trials [71].

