## 4. Materials and Methods: Data Collection, Management, and Analysis

### 4.1. Data Collection Methods

Data of the clinical trials (F_clin_, W_clin_) will be collected on about 336 subjects at four measurement time points (t0, t1, t2, t3) at the DoSS. The feasibility of the data collection methods has been tested in pilot trials. The data will be collected in separated and protected premises by qualified staff using reliable and validated instruments with standardized procedures. The staff will be thoroughly instructed and trained on all measurements in a standardized manner. The data collection will be done using a case report form for each study participant. The study staff will carefully complete this form during the medical examinations, and the study director will subsequently review it to ensure high data quality. All data will be digitized and subjected to final plausibility checks. The system usage data collection methods are described in the study protocol of the online trials [71].

Various measures are planned to promote participant retention and complete follow-up to make data sets as complete as possible. First, for successful trial participation, the study participants will receive free medical examinations, an activity tracker (Fitbit Charge 3^TM^), a shopping voucher, discount vouchers, and free access to the current version of the TK-HC. Moreover, the participants will be reminded of each medical examination, and all examinations will be scheduled in advance. Furthermore, participant retention and usage behavior data will be monitored. The reasons for non-retention and non-adherence will be documented for data analysis and interpretation. If subjects do not adhere to the intervention protocols, all outcome data will still be assessed. For data analysis, however, non-adherent participants will be considered by including the usage behavior data.

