According to the intention-to-treat (ITT) principle, all randomized cases will be included. In addition, only cases that have followed the per-protocol (PP) principle will be analyzed. While for ITT analysis, missing values will be imputed, in PP (complete case) analysis, only study participants with no missing values for the corresponding outcome will be analyzed. The ITT and PP analysis will be compared. An assessment of completed measurement time points will be used to test whether study participants who have completed all medical examinations differ in the corresponding outcome. Multiple imputation will be used to impute missing data in the ITT analysis. Influx and outflux statistics will be applied to identify factors that will serve as auxiliary variables for the imputation model. Sensitivity analysis will be performed to compare imputed with not imputed data.

The usage behavior data will be analyzed between the intervention and control group and within the intervention group. The analysis between the study groups will be done descriptively. For the analysis within the intervention group, the outlined model will be modified. Therefore, the group variable will be omitted, and a variable that codes usage behavior will replace the group variable in the model on level 2.

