### 5.2. Harms

No particular risks are expected in the context of the clinical trials (F_clin_, W_clin_). In rare cases, skin irritation or infection of the puncture site can occur after blood uptake. Furthermore, muscle soreness can occur in the following days after physical fitness assessments or training sessions of the health programs. No other risks are expected.

Apart from that, the study participants will have to agree to the inclusion and exclusion criteria, undergo a detailed screening, and, in case of health problems or diseases, provide a medical certificate attesting their ability to participate in the trial and the health program. Moreover, the potential risks were reviewed by the Ethics Committee of the University of Freiburg and the principal medical investigator of the study.

Adverse and any other events will be documented in a standardized way at the medical examinations. The study participants will be asked to inform the study staff if any event occurs in the interim study phases. Adverse events will be reported to the principal medical investigator of the study and the entire project team. If any event occurs, the study participants will be able to cancel, interrupt, or repeat the medical examinations. They will also have the possibility to cancel, interrupt, or modify the health program. If necessary, immediate care and treatment measures will be initiated by the principal medical investigator. He will also be able to terminate participation prematurely if health problems occur that partially or entirely exclude participating in the trial and the health program. Travel accident insurance, including stays on-site, will be arranged for all study participants.

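### Section 4.2, read literally, lets inability to follow the programme alone end outcome follow-up, in conflict with Sections 2.3.2, 4.1 and 5.2

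*Protocol article*

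**What the plan says.** **Termination, Section 4.2 (Data Management).** The principal medical investigator may "terminate participation prematurely if health impairments occur that partially or entirely exclude the ability to participate in the trial or the health program". The consequences are set out straight afterwards. On contact details the section states: "In such a case, the personal data will be deleted immediately". Measurements made up to that point are kept without identifiers and still analysed. For the time after termination the rule is: "No further data will be collected". The section applies the same handling to a person who leaves the trial but keeps using the programme. It does not mention the reverse case, a person who stops the programme but stays in the trial.

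**Termination, Section 5.2 (Harms).** The same power is stated again, but here the investigator may "terminate participation prematurely if health problems occur that partially or entirely exclude participating in the trial and the health program".

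**Stopping the programme only.** Section 2.3.2 treats this as an event of its own: "Criteria for discontinuing, interrupting, or modifying the allocated intervention are defined as feeling unwell, worsening health status, illnesses, diseases, injuries, harms, adverse events", with withdrawal as a further ground. Section 5.2 likewise lets participants stop, pause or change the programme, and deals with the examinations in a separate sentence.

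**Follow-up after non-adherence, Section 4.1.** "If subjects do not adhere to the intervention protocols, all outcome data will still be assessed". No exception is made for health reasons.

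**Analysis, Section 4.3.** "According to the intention-to-treat (ITT) principle, all randomized cases will be included". Missing values in that analysis are multiply imputed, and the sensitivity analysis named for this compares imputed with non-imputed data.

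**The concern.** A participant who can no longer follow the programme because of an injury or illness, but could still attend some examinations, falls under two rules. Section 4.1 keeps that person in outcome assessment. Section 4.2 allows the person to be removed, contact data included, so the loss cannot be undone. Staff at the site could apply either rule in good faith.

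At stake are outcomes at t1 to t3 that could have been measured. In W_clin the primary outcome is body weight, which many people unable to use the programme could still provide. The reason for the loss is health-related. It could also differ between arms, because one arm receives a training or diet programme and the other receives reading material. The later course of the event behind the termination could also be lost, because Section 5.2 documents events at the examinations and by participants' own reports, and both end once participation and contact end.

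**Working it through.** **1. The rules side by side**

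| Situation | Section | Outcome follow-up |
|---|---|---|
| Participant does not follow the programme | 4.1 | continues |
| Programme discontinued, interrupted or modified for health reasons | 2.3.2, 5.2 | not said to end |
| Health impairment partly or wholly rules out trial *or* programme | 4.2 | may be ended; personal data deleted |
| Health problem partly or wholly rules out trial *and* programme | 5.2 | participation may be ended |

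Inability confined to the programme meets the *or* condition in the third row. On its plain reading it does not meet the *and* condition in the fourth. It also fits the first two rows, where assessment continues or is not said to stop. The conflict is therefore between the follow-up rules, and the trigger itself is worded in two ways.

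**2. The plan's own figures (Section 2.6)**

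Inputs: d = 0.45 and 0.50, alpha 0.05 (taken as two-sided, which reproduces the figures), power 0.80, dropout 15%. A two-sample t-test gives 78.5, so 79 per group (F_clin), and 63.8, so 64 per group (W_clin). With dropout, 79/0.85 = 92.9, so 93, and 64/0.85 = 75.3, stated as 75. The figures reproduce, and none is disputed on this point. The allowance is 93 − 79 = 14 losses per arm in F_clin and 75 − 64 = 11 in W_clin.

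**3. What extra losses could do (assumptions, not document figures)**

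The documents give no rate of health-related termination. Let q be the excess proportion terminated in one arm only, and δ the amount in SD by which their unseen outcomes are worse than the imputed values. Then bias in the group difference = q × δ.

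| q | δ | Bias (SD) | Share of d = 0.45 | Share of d = 0.50 |
|---|---|---|---|---|
| 0.02 | 0.25 | 0.005 | 1% | 1% |
| 0.05 | 0.50 | 0.025 | 6% | 5% |
| 0.10 | 1.00 | 0.10 | 22% | 20% |

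The bias favours the arm with the excess losses. The standard error of the difference is about √(2/79) = 0.16 SD in F_clin and √(2/64) = 0.18 SD in W_clin, so even the top row of assumptions stays below one standard error. That row also means 0.10 × 93 = 9.3 excess terminations in one F_clin arm, against a planned allowance of 14 losses from all causes.

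On precision: if total dropout were 20%, 25% or 30% instead of 15%, power would be about 0.78, 0.75 or 0.72 in both trials. Nothing in the documents says that dropout will reach those levels.

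**4. Can the planned analysis detect the problem?**

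Comparing imputed with non-imputed results shows how much the imputation changes the answer. Standard multiple imputation assumes that missingness is explained by observed data. The comparison does not vary that assumption, so it does not test a mechanism that depends on the unseen outcome.

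**The case against.** The strongest reply is that Section 4.2 gives a discretion and prescribes nothing automatic. Milder routes exist: Sections 2.3.2 and 5.2 allow the programme to be changed or stopped on its own, and Section 2.4.2 reschedules examinations when a participant is unwell. The *and* wording in Section 5.2 suggests that only a person unable to do either was meant. All of this stands, and it makes termination for a programme-only problem one permitted reading and not a settled rule. It does not remove the conflict, because the wording with the data consequences attached is the broad one.

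Three stronger readings are tempting, and the documents do not support them.

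- *A reader might infer that the ITT rule is contradicted.* It is not. Randomized cases stay in, data already collected are kept, and missing values are imputed.
- *A reader might infer that the gaps will be filled from healthy completers, so that bias is certain.* The text does not say so. Earlier measurements of the same person are retained, auxiliary variables are to be selected for the imputation model, and reasons for non-retention are recorded. Participants are predominantly healthy and few harms are expected. Informative missingness is a plausible risk that the documents do not demonstrate.
- *A reader might infer that the adverse events go unrecorded.* Section 5.2 requires them to be documented and reported. Only follow-up after termination may be missing.

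It is also fair to say that continued attendance helps F_clin less. Its primary outcome is a 12-minute run to near-maximal effort, which an injured participant may not be able to do. Secondary outcomes could still be obtained.

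**Conclusion.** The point holds as an inconsistency in the follow-up rules. Section 4.2 permits outcome collection to end, and personal data to be deleted, when only participation in the programme is affected. That conflicts with Section 4.1, with the trigger as worded in Section 5.2, and with the separate handling of the programme in Sections 2.3.2 and 5.2. The consequence is avoidable missing outcomes, possibly related to health and arm, which the named sensitivity comparison would not probe.

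The size of any bias is unknown. The range of 0.005 to 0.10 SD rests wholly on the assumed excess rate, the assumed gap and the assumed confinement of the excess to one arm. It is an illustration and not an estimate. No figure in the article is wrong on this point, and which clinical stopping rule should apply is not judged here.

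**What to change.** Reconcile Sections 2.3.2, 4.1, 4.2 and 5.2, including the *or*/*and* discrepancy, so that:

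- stopping or changing the programme for health reasons does not by itself end outcome collection or trigger deletion of contact data;
- such participants keep their scheduled t1 to t3 visits for whatever assessments the medical investigator permits;
- deletion and the end of data collection apply to withdrawal of consent, or to termination of trial participation itself.

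The investigator's power to stop the programme or to end trial participation on health grounds is unchanged. For participants already terminated, report the number of health-related terminations by arm; Section 4.1 already provides for recording reasons for non-retention.

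The cost is an amendment to the protocol and consent wording. The visits are already planned and budgeted. Because data collection began in January 2020 and is to finish by spring 2022, the change can affect only the remaining visits, and contact data already deleted cannot be recovered.

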### 4.3. Statistical Methods

For all analyses, the IBM SPSS Statistics software (Version 28.0.0.0) (IBM Corporation, Armonk, NY, USA) [113] as well as R (Version 4.0.5) [114] and RStudio (Version 1.4.1106) [115] will be used. All primary and secondary outcomes will be assessed on a metric scale level at all measurement time points. Therefore, linear mixed models (LMMs) will be used for statistical analyses of all outcomes. In the repeated measured data, the time points will be nested within cases, so the cases will be the cluster variable. The time points will enter the model as a continuous variable from baseline (0) to the end of the study (3). Random effects for intercept will be estimated. Degrees of freedom will be calculated with Satterthwaite’s method implemented in a specific R package (lmerTest). The basic model will consist of a cross-level interaction and random effects for intercept and slopes.

Level 1:

$Outcome=\beta_{0j}+\beta_{1j}*time+\beta_{nj}*X_{nj}+r_{ij}$

Level 2:

$\beta_{0j}=\gamma_{00}+\gamma_{01}*group+\gamma_{0n}*Z_{0n}+u_{0j}$

$\beta_{1j}=\gamma_{10}+\gamma_{11}*group$ $+u_{1j}$

The cross-level interaction will be between time and the dichotomous group variable (intervention vs. control group). The fixed effect $\gamma_{10}$ will represent the average change over time, while the cross-level interaction $\gamma_{11}$ will represent the difference in change between both study groups. Possible covariates or confounding variables, such as age and gender, can enter the model at the placeholder $X_{nj}$ on level 1 or $Z_{0n}\;$ on level 2.

To analyze short- and medium-term effects, the metric scale time point variable will be changed to a factor variable. Pairwise comparisons will be used with correction for multiple testing to estimate differences between each measurement time point. We will test group differences on time points t1, t2, and t3 as between-group contrast. Within each group, we will compare baseline with program completion (t0 vs. t1) and baseline with follow-up (t0 vs. t2). Additionally, we will contrast program completion with follow-up (t1 vs. t2) and change between follow-up and the end of the study (t2 vs. t3). Moreover, there is no need to account for multiple testing for the two primary outcomes as the two clinical trials (F_clin_, W_clin_) are considered as two independent trials.

According to the intention-to-treat (ITT) principle, all randomized cases will be included. In addition, only cases that have followed the per-protocol (PP) principle will be analyzed. While for ITT analysis, missing values will be imputed, in PP (complete case) analysis, only study participants with no missing values for the corresponding outcome will be analyzed. The ITT and PP analysis will be compared. An assessment of completed measurement time points will be used to test whether study participants who have completed all medical examinations differ in the corresponding outcome. Multiple imputation will be used to impute missing data in the ITT analysis. Influx and outflux statistics will be applied to identify factors that will serve as auxiliary variables for the imputation model. Sensitivity analysis will be performed to compare imputed with not imputed data.

The usage behavior data will be analyzed between the intervention and control group and within the intervention group. The analysis between the study groups will be done descriptively. For the analysis within the intervention group, the outlined model will be modified. Therefore, the group variable will be omitted, and a variable that codes usage behavior will replace the group variable in the model on level 2.

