All primary and secondary outcomes will be assessed at four measurement time points (t0: 0 weeks, t1: 12 weeks, t2: 6 months after t1, t3: 12 months after t1), each taking about 4–5 h (F_clin_), and 2–3 h (W_clin_), at the DoSS. All medical examinations will be carried out at the same time of day using standardized procedures by trained and qualified sports and nutritional science and medical staff in separated rooms to protect privacy. The study participants will fast (meal and drinks, nicotine consumption: ≥12 h, alcohol consumption and exercise: ≥48 h). In addition, they will have to sleep sufficiently the night before and will have to be in a current state of good health. These criteria will be checked individually via an anamnesis at the beginning of each medical examination, in which current sensitivities, general habits and disorders of sensitivities, and medication, illnesses, and diseases will also be assessed. Moreover, in case of health problems or diseases, the medical certificate from a general practitioner attesting to the ability to participate in the trial and the health program will be checked, and adverse events will be documented. If these examination conditions are not met, or the examination cannot be performed as scheduled for other reasons, such as coronavirus infection, the examination will be rescheduled as soon as possible, depending on the individual’s state of health. Any rescheduled appointments will be carefully documented for consideration in the data analysis. Furthermore, at the beginning of each measurement, there will be a detailed introduction, instruction, and demonstration of the respective measurement procedure. In case of pain, discomfort, or complications, the measurement will be stopped immediately and, if necessary, repeated. An overview of all primary and secondary outcomes can be found in Table 1.

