### 2.6. Sample Size

The sample sizes of the clinical trials (F_clin_, W_clin_) were calculated with regard to the long-term effect (t0–t3) of the respective primary outcome (F_clin_: VO_2_max, W_clin_: body weight) using G*Power software (Version 3.1) (Heinrich-Heine-Universität Düsseldorf, Düsseldorf, Germany) [109]. Based on comparable studies [50,110,111], effect sizes of Cohen’s *d* = 0.45 (F_clin_) and *d* = 0.50 (W_clin_), as well as a significance level of 0.05 and a statistical power of 0.80 were assumed. For the fitness trial (F_clin_), this resulted in a required case number of *n* = 79 for both the intervention and control groups. For the weight loss trial (W_clin_), the required case number was *n* = 64 for both study groups. Allowing for an additional dropout rate of 15% in each trial, the total target sample size was found to be *n* = 186 (93 + 93) (F_clin_) and *n* = 150 (75 +75) (W_clin_). Due to limited resources, there are no plans to exceed these sample sizes. Details can be found in the study protocol of the online trials [71].

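### The random effects are stated inconsistently and the factor-time model has no estimable covariance as written; a random intercept alone would distort the standard errors of change

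*Protocol article*

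**What the plan says.** All of this is in section 4.3 (Statistical Methods) of the protocol article.

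- On estimation: "Random effects for intercept will be estimated".
- Two sentences later: "The basic model will consist of a cross-level interaction and random effects for intercept and slopes". The displayed level-2 equation for the time coefficient agrees with this, because it carries a person-specific deviation u_1j.
- In that basic model, time is a numeric index running from 0 to 3.
- For short- and medium-term effects, "the metric scale time point variable will be changed to a factor variable". The section does not say which random effects remain after this change.
- The factor version carries the between-group tests ("We will test group differences on time points t1, t2, and t3 as between-group contrast") and four listed within-group comparisons: t0 vs t1, t0 vs t2, t1 vs t2 and t2 vs t3. The pairwise comparisons are to be corrected for multiple testing.

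Section 2.4.2 gives the visits: "t0: 0 weeks, t1: 12 weeks, t2: 6 months after t1, t3: 12 months after t1". Section 2.6 bases the sample size on the long-term t0–t3 effect. No SD, slope variance, residual variance or within-person correlation is given anywhere.

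**The concern.** Two analysts could fit different models and both cite the plan. The question is most open in the factor-time version, because replacing numeric time by a factor in the written equations gives each person a separate deviation at each factor level. With one value per visit, that model cannot be estimated beside a residual. Something has to be dropped, and the intercept sentence offers the shortest route. Section 3.2 adds that the analysts will not be blinded, so the choice may be made with group membership known.

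A random intercept alone imposes one correlation on every pair of visits. It treats t0 and t1 (12 weeks apart) as no more alike than t0 and t3 (about 15 months apart). If participants differ in their trends, the model averages short and long intervals. Standard errors then come out too large for changes between neighbouring visits and too small for change over the whole study. Short-term claims lose power, and long-term claims of change gain false positives.

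**Working it through.** **The plan's own figures.** The plan states no type I error beyond the planning values ("a significance level of 0.05 and a statistical power of 0.80 were assumed"). A two-sided two-sample t-test with those values and d = 0.50 gives 64 per arm for the weight trial, and d = 0.45 gives 79 for the fitness trial, as stated. The number per arm cancels from the ratios below.

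**Identifiability.** A 4×4 covariance matrix has 4×5/2 = 10 distinct elements.

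- One random effect per factor level: 10 variances and covariances + 1 residual = 11 parameters. A rank check gives 10, so this is not identifiable.
- Factor time in the fixed part, with a random intercept and a random slope on numeric time: 3 + 1 = 4 parameters, rank 4, identifiable.
- Unstructured covariance without a separate residual: 10 parameters, identifiable.

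**Size of the error under a random intercept only.** The variances are assumptions for body weight: person SD 12 kg (variance 144), residual SD 1.5 kg (e² = 2.25), linear drift SD s = 0.10 to 0.25 kg/month, independent of the starting level. Visits are at 0, 2.76, 8.76 and 14.76 months. Data are balanced and unadjusted for multiplicity.

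The mean time is 6.57 months and the sum of squared deviations is 129.55. The within-person variance that the random-intercept model settles on is

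v = e² + s² × 129.55 / 3.

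For a change between visits d months apart, the model uses 2v and the true variance is 2e² + s²d². The standard-error ratio is R = √(2v / (2e² + s²d²)), and the type I error is 2 × [1 − Φ(1.96 R)].

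With s = 0.25: v = 2.25 + 0.0625 × 43.18 = 4.949, so 2v = 9.898.

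- t0–t1 (d = 2.76): true 4.5 + 0.476 = 4.976; R = 1.41; error 0.6%.
- t1–t2 and t2–t3 (d = 6): true 4.5 + 2.25 = 6.75; R = 1.21; error 1.8%.
- t0–t2 (d = 8.76): true 4.5 + 4.796 = 9.296; R = 1.03; error 4.3%.
- t0–t3 (d = 14.76): true 4.5 + 13.616 = 18.116; R = 0.74; error 14.7%.

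With s = 0.10: v = 2.682, so 2v = 5.364.

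- t0–t1: true 4.576; R = 1.08; error 3.4%.
- t1–t2 and t2–t3: true 4.86; R = 1.05; error 4.0%.
- t0–t2: true 5.267; R = 1.01; error 4.8%.
- t0–t3: true 6.679; R = 0.90; error 7.9%.

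The same ratios apply within an arm and to the difference in change between arms.

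**Group difference at a visit.** The model uses the average total variance over the four visits. The true variance at month t is 144 + 2.25 + s²t². With s = 0.25 the average is 150.97, against true values of 146.73 (t1), 151.05 (t2) and 159.87 (t3). The errors are 4.7%, 5.0% and 5.7%. With s = 0.10 they are 5.0%, 5.0% and 5.1%.

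**Linear slope, if its random slope were dropped.** The slope on the index 0–3 has weights (−1.5, −0.5, 0.5, 1.5)/5. Applied to the visit months these give 25.14/5 = 5.028. The model variance is v/5 and the true variance is e²/5 + s² × 5.028².

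- s = 0.25: 0.990 against 0.45 + 1.580 = 2.030; R = 0.70; error 17.1%.
- s = 0.10: 0.536 against 0.703; R = 0.87; error 8.7%.

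**Linear slope, with the random slope kept as written.** Simulation with 64 per arm, 6000 runs and trends linear in the visit index gave a type I error of 4.4–5.3%.

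**The case against.** The strongest reply is that the main model is specified. The intercept sentence does not say that nothing else is random, and both the basic-model sentence and the equation include the slope. This stands: the test of the group difference in change, read by its equation, holds its level.

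A reader might infer that the plan as a whole carries a type I error of 14–17% for body weight. The documents do not support that, for four reasons.

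- The 17% belongs to the slope test in the continuous-time model, where the random slope is written and estimable. The factor-time difficulty cannot produce it.
- The 14.7% belongs to a t0–t3 change. That is not among the four listed within-group comparisons. It enters only under the general statement on pairwise comparisons, which also applies a multiplicity correction.
- The between-group tests that the plan names at t1, t2 and t3 are little affected.
- All these percentages rest on variances that the document does not give. With no slope variance the error is 5%. For trends linear in the visit index, the slope test without its random slope has a limit of about 26%.

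Nor does factor time rule out all random time effects, since a slope on numeric time or an unstructured covariance remains estimable. No fallback to a random intercept is stated; it is an inference from the intercept sentence.

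It can also be said that covariance details belong in an analysis plan that is not shown. That would cover silence. Here the article states the random effects twice in different terms and then changes the time variable in a way that its own equations cannot follow.

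**Conclusion.** The point holds at moderate severity. The random effects are described inconsistently, and the factor-time model cannot be run with the written random time effect carried through to each level. The replacement is left open, and one sentence permits a poor one.

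If a random intercept alone were used and participants differ in trend, the listed comparisons t0–t1, t1–t2 and t2–t3 would get standard errors about 1.05 to 1.4 times too large. Their type I error would be 0.6–4%, with power lost. A t0–t3 change would be tested at 8–15% instead of 5%. These figures are conditional on the assumed person SD of 12 kg, residual SD of 1.5 kg and drift SD of 0.10 to 0.25 kg/month, on linear personal trends, and on complete data. The direction of the errors follows from the trends differing between people; the size follows from the assumptions.

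**What to change.** 1. Delete or correct the intercept sentence so that the continuous-time model always includes the random intercept and the random slope, as its equation shows.
2. For the factor-time model, specify an unstructured 4×4 within-person covariance with no separate residual, which the SPSS software already named can fit. At the least, keep the random intercept and the slope on numeric time beside the factor fixed effects.
3. State in advance a simpler structure to use if the chosen one does not converge, so that the choice is not made by unblinded analysts with the data in hand.

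The cost is a few lines of analysis-plan wording. The unstructured form has 10 covariance parameters, against 2 for a random intercept with residual and 4 for intercept and slope. The target samples of 150 and 186 participants support that easily. No change to sample size, visits or data collection is needed.
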